#### Sub-studies

Two sub-studies will be performed. The first sub-study will examine the false-negative rate for both home-based albuminuria screening strategies. Around 500 subjects per screening method who have a negative first home-based albuminuria screening test will be invited to perform an additional test, to examine the false-negative rate. This additional test will be done via the UCD, as this test provides a quantitative, exact ACR value as usual in clinical care. There is no need for further action, if this second test is also negative. If this second test is positive, the participant is sent a third test to confirm the result.

The second sub-study will examine whether lowering the cut-off value for the ACR increases the yield of the home-based screening. All subjects of the UCD-method with an ACR in their first test between 2–3 mg/mmol are invited for a second home-based albuminuria test (again with the UCD). If the ACR of the second test is negative (ACR <30 mg/g), there is no need for further action. If the ACR of the second test is positive (ACR ≥30 mg/g), the participant is invited for a third home-based test. If the third test is negative, no further action is undertaken. If the ACR of the third test is positive, the participant is invited for the elaborate screening.

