#### Home-based screening

All randomized individuals receive an invitation to participate in the home-based screening via mail, along with information on possible advantages and disadvantages of participation, and the assigned home-based screening method including test instructions. Participants are instructed to use midstream early morning void urine (EMV) for the test, and to postpone the home-based urine test in case of fever, urinary tract infection, pregnancy, menstruation, or having exercised intensively the day before. Two home-based albuminuria screening strategies are examined:

*UCD-method*. Individuals randomized to the UCD-method receive a PeeSpot UCD (Hessels+Grob B.V., Deventer, The Netherlands) [17,18]. This device consists of a holder containing a urine absorption pad in a transport tube (Fig 3). The urine absorption pad is a felt containing a dried hygroscopic polymer. Subjects hold the absorbent pad in their urine stream that absorbs approximately 1.2 ml of urine to collect a portion of urine. The participants insert the holder with the pad containing urine back into the tube, place the tube in a safety bag, and send this safety bag to a central laboratory by surface mail together with a signed informed consent form. A dried preservative in the urine absorption felt prevents bacterial growth during four days at room temperature. Participants are instructed to collect and send their urine sample on the same day, Monday through Thursday, and only during weather conditions that allow sending biosamples by mail (temperature between 0°C and 25°C). After receiving the sample in the central laboratory, the tube is centrifuged (5 minutes, 1800G) to release the urine into the tube with 100% albumin recovery. Urinary albumin and creatinine concentrations are measured by immuno-turbidimetry and enzymatically, respectively, on a cobas c502 analyzer (Roche Diagnostics, Almere, The Netherlands), with for albumin a lower limit of detection of 3 mg/L and intermediate precision of 4.2%, and for creatinine a lower limit of detection of 100 μmol/L and intermediate precision of 2.1%. ACR is reported as mg/mmol.

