**Fig 4 pone.0279321.g004:**
[figure not shown]
App test kit and its components to be used in the App-method. Abbreviations: App, smartphone application.

If the first test result is negative (ACR < 3 mg/mmol for the UCD-method; ACR <30 mg/g for the App-method), no further examinations are needed. However, if the first test result indicates increased albuminuria, participants are sent a second test kit for confirmation. When the result of the second test is negative, a third test is sent. In case the initial increased albuminuria result is confirmed by either the second or third test, the participant is invited for a visit to a screening facility where an elaborate screening follows. Reminders are sent to non-participating subjects three and six weeks after the initial invitations.

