### Sample size

The sample size of this study is calculated to be able to show a 5% difference in participation rate between the two screening strategies, with assumptions based on previous data [7], including an overall participation rate for the home-based screening of 50%, 8% of the participants having elevated ACR, of which 90% will be confirmed by the confirmatory tests, and a participation rate in the elaborate screening of 90%. Adopting a power of 80% and a 2-sided alpha of 0.05, a minimum of 15.032 individuals are to be invited to participate to detect this 5% difference in participation rate between the two screening strategies. This number of individuals also allows discerning a significant difference between both screening strategies in the number of individuals with elevated albuminuria diagnosed with at least one newly discovered CKD or CVD risk factor.

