There are other important considerations that merit attention. First, this screening study is primarily focused on early identification of subjects with CKD. Therefore, not all subjects with CVD risk factors will be identified. Previous epidemiological analyses showed that people with newly discovered CVD risk factors, but no elevated albuminuria, on average have an absolute risk for CVD that does not merit start of cardioprotective treatment [11]. In contrast, subjects with newly discovered CVD risk factors and elevated albuminuria in general have such a high CVD risk that start of preventive treatment is indicated [11]. These data suggest that a screening primarily directed at discovering subjects with elevated albuminuria may be effective in discerning high-risk subjects for whom screening will have therapeutic consequences. Future studies could further investigate this. Second, the present study investigates the effectiveness of a single screening. Therefore, this study cannot directly demonstrate potential benefits regarding renal and CV event outcomes for repeated screening. However, the effectiveness of a repeat screening strategy can be modeled in the cost-effectiveness analyses. Third, it is assumed that the potential harms of the study are limited, because our screening strategy does not include invasive procedures. In addition, the psychological burden should be limited, because the diagnosis of CKD is based on an initial positive test that has to be confirmed, which by definition implies CKD. To further reduce potential psychological distress induced by the screening, all subjects will receive a brochure with detailed information including potential benefits and harms of participation. More information can be found on a dedicated internet site (www.niercheck.nl). Lastly, the UCD screening method uses the ACR cut-off of 3 mg/mmol for elevated albuminuria, whereas the App uses an ACR cut-off of 30 mg/g, which are not exactly equal. If needed, after completion of the study the results of the UCD-method can be modeled as if they were also reported in mg/g to evaluate any consequences and to allow a fair comparison with the App-method.

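### Sub-study 1 yields a UCD repeat-positive proportion in one arm and App–UCD disagreement in the other; neither is a false-negative rate, and their difference can be biased in either direction

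*Protocol article*

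**What the plan says.** The Sub-studies section sets the aim: "The first sub-study will examine the false-negative rate for both home-based albuminuria screening strategies". It then describes the sample: "Around 500 subjects per screening method who have a negative first home-based albuminuria screening test will be invited to perform an additional test". The retest device is the same in both arms: "This additional test will be done via the UCD, as this test provides a quantitative, exact ACR value as usual in clinical care". A negative retest ends follow-up. For a positive one, "If this second test is positive, the participant is sent a third test to confirm the result".

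Three other places bear on this:

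- Home-based screening gives the limits for a negative first test: "ACR < 3 mg/mmol for the UCD-method; ACR <30 mg/g for the App-method". The Discussion acknowledges that the UCD uses 3 mg/mmol, "whereas the App uses an ACR cut-off of 30 mg/g, which are not exactly equal".
- Home-based screening says that the UCD tube is centrifuged "to release the urine into the tube with 100% albumin recovery".
- The Discussion names 24-hour albumin excretion as the reference method and sets it aside as impractical at this scale. No other independent reference is described for people with a negative first test.

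**The concern.** A false-negative rate needs a reference other than the test under study. In the UCD arm the reference is a second UCD. Any error that the device repeats in the same person, such as loss in the pad or in the post, occurs again at the retest and is never counted. In the App arm the reference is a different method. Two unlike quantities would therefore be reported under one name.

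The name is loose for a second reason. Only people with a negative first test are sampled, so the result is a proportion among negatives. A false-negative rate has the truly elevated as its denominator.

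At stake is what may be said about missed albuminuria. A low UCD figure could be taken as evidence that the UCD misses little, and the difference between arms as evidence on which device misses more. The design supports neither reading. Cost-effectiveness is to be modelled from study data, so either figure could also enter the model as a miss rate, although the article does not say so.

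**Working it through.** The article gives no expected rate, power or precision for sub-study 1, so there is no stated figure to reproduce. The check concerns what each figure contains and which way it moves.

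**1. The two quantities**

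- UCD arm: P(UCD retest ≥ 3 mg/mmol | first UCD < 3 mg/mmol).
- App arm: P(UCD retest ≥ 3 mg/mmol | first App < 30 mg/g). The retest cut-off of 3 mg/mmol is assumed, as the UCD's usual limit.
- Taking 8.84 mg/g per mg/mmol (an assumption, from the molar mass of creatinine), 3 × 8.84 = 26.5 mg/g. The App arm therefore compares a first test at 30 mg/g with a retest at about 26.5 mg/g.

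**2. Direction under systematic under-reading**

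Suppose that every UCD reads a fraction λ of the true value. Then a UCD below 3 means a true value below 3/λ. With λ = 0.8 the effective limit is 3/0.8 = 3.75 mg/mmol at both UCD tests. People with a usual value between 3 and 3.75 tend to read negative twice and go uncounted. In the App arm only the retest limit moves: a person must go from below the App's limit to at least 3.75, which is harder. The App figure therefore falls faster.

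**3. Size, first model**

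Assumptions, none from the article: 7% with usual ACR ≥ 3 mg/mmol; log-normal between-person SD 1.1; day-to-day SD 0.3 or 0.5 log units; 5% assay error; one cut-off for all tests; App unbiased. Positive means that the second and third tests, both UCD, are positive. Second decimals carry small simulation error.

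| Day-to-day SD | UCD loss | UCD figure | App figure | Same UCD-negatives, unbiased retest |
|---|---|---|---|---|
| 0.3 | 0% | 0.95% | 0.95% | 0.95% |
| 0.3 | 10% | 0.81% | 0.56% | 1.30% |
| 0.3 | 20% | 0.67% | 0.30% | 1.76% |
| 0.5 | 10% | 1.25% | 1.05% | 1.74% |
| 0.5 | 20% | 1.04% | 0.70% | 2.06% |

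At SD 0.5 with no loss the UCD figure is 1.47%. At SD 0.3 and 20% loss, App minus UCD is 0.30 − 0.67 = −0.37 points, although the App is accurate.

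Now remove the loss and give each method its own error that persists within a person (SD 0.1 to 0.3 log units, equal for both). The App figure becomes about 1.03 to 1.86 times the UCD figure, although the true missed shares are equal. With both mechanisms at 20% loss and day-to-day SD 0.3, the App/UCD ratio is 0.80 at persistent SD 0.2 and 1.20 at 0.3. The sign is not determined.

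**4. Size, second model**

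Here 8% are positive at the first test, matching the Sample size assumption of "8% of the participants having elevated ACR". Assumed log-SDs are 0.9 between and 0.4 within persons, with App error 0.3. The App limit is 30 mg/g, and a single positive UCD retest counts.

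| UCD reads low by | UCD figure | App figure | UCD-negatives whose own mean is ≥ 3 mg/mmol |
|---|---|---|---|
| 0% | 3.63% | 4.28% | 1.56% |
| 10% | 3.05% | 3.19% | 2.02% |
| 20% | 2.48% | 2.23% | 2.60% |
| 50% | 0.96% | 0.41% | 4.66% |

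The planned UCD figure falls while the true share missed rises. The order of the two arms reverses between 10% and 20% loss, while the App's own true share stays at about 2.3%. The UCD figure also falls at every step in two other variance settings (4.91% to 1.43%, and 3.47% to 1.30%, from no loss to 50%).

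Sporadic under-reading, independent between samples, behaves differently: the UCD figure stays about flat (at most +0.09 points) or falls.

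On the denominator: in the unbiased row, 1.56% of UCD-negatives are truly elevated, whereas 23.1% of the truly elevated are missed at the first test.

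**5. Precision**

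If all 500 people invited in an arm respond, 1% is 5 events, exact 95% CI 0.33% to 2.32%; 3% is 15 events, 1.69% to 4.90%.

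**The case against.** The strongest reply is that the concern is partly hypothetical and small. The article states full recovery and cites device sources that are not available here. Recovery is a question for device validation, and day-to-day variation is a real cause of misses with a single void. The loss-induced shifts in the UCD figure in the first model, from 0.95 − 0.81 = 0.14 to 1.47 − 1.04 = 0.43 points, are 0.7 to 2.2 people in 500, below what the sub-study can see.

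Much of this stands. No under-reading is shown, and the sizes rest on assumed variances. But the shift in the reported figure understates the problem. What matters is the distance from what an independent retest would show: at SD 0.3 and 20% loss, 1.76 − 0.67 = 1.09 points, or about 5 people in 500. The labelling point holds even with no loss.

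Four stronger readings are tempting and are not supported:

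- That the comparison is tilted against the App. This holds for person-persistent method error and for the cut-off gap; systematic UCD loss tilts it the other way.
- That any UCD under-reading lowers its own figure. Only systematic under-reading reliably does.
- That the plan ranks the devices on false negatives. Sub-studies states no test, ranking or decision rule. The comparison promised in the Discussion covers user-friendliness, willingness to participate, yield and cost-effectiveness.
- That leaving the third-test device unnamed is a defect. A condensed article may leave this to the full protocol.

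**Conclusion.** The point holds as a limit on inference. The UCD arm gives a test-retest proportion among first-test negatives, which cannot reveal systematic UCD error and would fall if such error existed. The App arm gives a different quantity. Their difference can be biased either way and, under systematic UCD loss, can be negative for an accurate App.

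The direction under systematic loss was the same in every variance setting tried. The magnitudes depend on assumed between-person, within-person and method variances that the article does not give. In the first model, with neither loss nor persistent method error and one cut-off throughout, the contrast between arms is undistorted. The matter affects a sub-study outside the listed primary and secondary outcomes and leaves the randomised comparison of participation and yield untouched.

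**What to change.** In Sub-studies:

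- Report the UCD-arm result as the repeat-positive proportion among UCD-negatives, and the App-arm result as the UCD-confirmed positive proportion among App-negatives, each with its confidence interval. The second label assumes that the third test is also a UCD; the report should state the device used.
- Use a common ACR cut-off. The App returns categories at 30 mg/g only, so the UCD values would be re-expressed in mg/g, which the Discussion already allows for. UCD first tests between about 26.5 and 30 mg/g count as positive at 3 mg/mmol and so fall outside the retested sample; the report should say so.
- Call neither figure a false-negative rate of the strategy, and do not interpret their difference as a difference in missed albuminuria.
- If either figure serves as a miss rate in the cost-effectiveness model, vary it in a sensitivity analysis for systematic UCD under-recovery.

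The cost is wording, a unit conversion and possibly one extra model scenario, with no new samples. The downside is a weaker claim about the UCD.

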### Outcomes

#### Primary outcomes

The primary outcomes are the participation rate and yield of the home-based screening, the elaborate screening, and the overall screening program (Fig 1). The outcomes will be assessed separately for each of the two home-based screening strategies. The participation rate is defined as the number of individuals completing the home-based screening, elaborate screening, and overall screening program relative to the number of invited individuals (with completion including the required confirmation tests). The yield of the home-based screening is defined as the number of individuals who test positive for albuminuria (at least two tests positive) relative to the number of participating individuals. The yield of the elaborate screening is determined as the number of participants with increased albuminuria and newly diagnosed or poorly controlled CVD or CKD risk factors (including hypertension, hypercholesterolemia, type 2 diabetes, and impaired kidney function.

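### Sub-study 2 classifies UCD repeat tests at 30 mg/g although the UCD arm works at 3 mg/mmol, and the primary yield wording does not keep sub-study positives out

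*Protocol article*

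**What the plan says.** **UCD arm, main pathway.** Under Home-based screening the plan states for the UCD that "ACR is reported as mg/mmol", and it sets the first-test cut-offs by arm: "If the first test result is negative (ACR < 3 mg/mmol for the UCD-method; ACR <30 mg/g for the App-method), no further examinations are needed". A positive first test is repeated, and confirmation by the second or third test leads to the elaborate screening. The Discussion again gives 3 mg/mmol as the UCD cut-off and 30 mg/g as the App cut-off, and says that they are not exactly the same.

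**Sub-study 2.** It takes only UCD participants with a first ACR of 2–3 mg/mmol and retests them with the UCD. For the second test: "If the ACR of the second test is positive (ACR ≥30 mg/g), the participant is invited for a third home-based test". For the third: "If the ACR of the third test is positive, the participant is invited for the elaborate screening"; no figure is attached to the third test. The Discussion describes this work as a sensitivity analysis in which the cut-off of the first test is lowered.

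**Primary yield.** Under Primary outcomes, home-based yield is "the number of individuals who test positive for albuminuria (at least two tests positive) relative to the number of participating individuals". Statistical analyses compares yield between the arms with a chi-square test.

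**The concern.** There are two linked problems.

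First, sub-study 2 asks what is gained by lowering the first-test cut-off. To answer that, the repeat tests must be judged as in the main UCD pathway. As written, the repeat cut-off changes too, and upward. A repeat value of 3.2 mg/mmol confirms albuminuria in the main UCD pathway but is negative in the sub-study. The added yield is then not comparable with the main UCD yield to which it would be added.

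Second, a sub-study 2 participant with positive second and third tests has two positive tests and is invited to the elaborate screening. The primary yield wording does not require the first test to be positive, so it literally admits this person. Sub-study 2 exists only in the UCD arm, so counting such cases would add to one side of a randomized comparison.

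**Working it through.** The plan gives no figure for the sub-study's yield and no ACR distribution, so there is no stated result to reproduce. The unit and direction follow from the text. The sizes are illustrations.

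**1. Unit conversion.** Creatinine molar mass is taken as 113.12 g/mol, a physical constant that is not in the document.
- 30 mg/g × 0.11312 g/mmol = 3.39 mg/mmol
- 3 mg/mmol ÷ 0.11312 = 26.5 mg/g
- 3.39 ÷ 3 = 1.13, so the sub-study's repeat cut-off is about 13% higher

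**2. Direction.** Anyone whose repeats are both at or above 3.39 mg/mmol also has both at or above 3 mg/mmol, and the reverse fails. The added yield at 30 mg/g therefore cannot exceed that at 3 mg/mmol, whatever the distribution. This holds even if only the second test is read in mg/g.

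**3. What recoding cannot recover.** A participant whose second test lies between 3 and 3.39 mg/mmol is negative under the sub-study rule and gets no third test. Recoding the stored values can reclassify the second test but cannot supply the third.

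**4. Planned numbers (Sample size).**
- Invited per arm: 15,032 ÷ 2 = 7,516
- Participants per arm: 7,516 × 50% = 3,758
- Confirmed yield: 8% × 90% = 7.2%
- Confirmed cases: 3,758 × 0.072 = 271

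**5. Illustrative size, first set.** Assumptions: log-normal ACR, 8% of first tests at or above 3 mg/mmol, between-person log-SD 0.8–1.0, within-person coefficient of variation 0.3–0.5, and every invited sub-study person completes the tests.
- First ACR of 2–3 mg/mmol: 7.0–9.6% of UCD participants
- Extra confirmed cases with repeats at 3 mg/mmol: about 28–33
- Extra confirmed cases with repeats at 30 mg/g: about 16–19
- Shortfall from the mixed unit: 33–47%
- Confirmation of first positives in this model: 65–82%, below the planned 90%

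**6. Illustrative size, second set.** With a within-person log-SD of roughly 0.15–0.25, confirmation comes near the planned 90%. The extra cases at 30 mg/g fall to about 7–12, and the shortfall from the mixed unit rises to 49–71%.

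**7. If sub-study positives were counted in primary yield.** With no true difference between arms and an added proportion *a*, the chance of a significant result favouring UCD is about Φ(*a*/SE − 1.96), with SE = √(2·p̄(1−p̄)/3,758). The nominal chance in that direction is 2.5%.
- 7 cases: *a* = 7/3,758 = 0.0019, SE ≈ 0.0060, chance about 5%
- 12 cases: *a* = 0.0032, SE ≈ 0.0060, chance about 8%
- 19 cases: *a* = 0.0051, SE ≈ 0.0061, chance about 13%

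With the simulated main yields of step 5 (5.2–6.6%) in place of 7.2%, the 16–19 cases raise yield by 6–10% relative, and the chance is 11–16%. A cruder range shows how much depends on the inputs. If 2–6% of participants fall in the band and 10–40% of them test positive twice, 8–90 cases are added. Yield then moves from 7.2% to 7.4–9.6%, and the chance runs from 5% to 96%.

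**The case against.** **The mg/g figure may be loose notation.** The Discussion names 30 mg/g and 3 mg/mmol together as the study cut-off, the sub-study selects in mg/mmol, and nothing shows that the laboratory applied 3.39 mg/mmol. This stands as a possibility. But the same Discussion says that the two are not exactly equal, and the sub-study text gives only the mg/g figure. The option to re-model UCD results in mg/g concerns the comparison with the App and does not replace third tests that were never sent.

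**Exclusion from primary yield is probably intended.** The main pathway starts from a positive first test that is then confirmed, the Discussion describes the diagnosis in the same way, and it calls the lower cut-off a sensitivity analysis. The full protocol or analysis plan may say so outright. This largely stands. What remains is that the stated primary definition does not carry the condition.

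**The App arm also has a route.** Sub-study 1 retests around 500 first-test negatives per method, and two later positives there also fit the wording. This stands. That route is roughly balanced between arms, and no invitation to the elaborate screening is stated for it. The imbalance is specific to sub-study 2.

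**A reader might infer that the sub-study and primary results are both already distorted, and that participation and cost comparisons are inflated for UCD.** The documents do not support this. Bias in yield arises only if the cases are counted. Against 7,516 invited per arm, 16–19 extra attenders at the elaborate screening would be 0.21–0.25 percentage points. No cost effect has been calculated, and each strategy is compared with standard of care. Home-based participation, on which the study is sized, is not shown to be affected.

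**Conclusion.** The unit inconsistency is on the page. If applied as written, it understates the added yield of a lower first cut-off relative to the main UCD pathway. The direction needs no assumption beyond the unit conversion. The size does: the two sets of assumptions give shortfalls of 33–47% and 49–71%, and neither should be quoted as an estimate.

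The primary-yield part is conditional. The literal definition admits UCD-only sub-study cases, and nothing in the article excludes them, but its other passages point to exclusion. If they were counted, the comparison would tilt towards UCD. Under the modelled distributions the chance of a false significant result in that direction would be about 5–16% instead of 2.5%, assuming full completion of the sub-study tests.

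This is a defect of consistency and definition that should be corrected before analysis. It does not show that the trial's main comparison is biased.

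**What to change.** - Reconcile the UCD cut-off and unit across Home-based screening, Sub-studies and the Discussion, so that all UCD results, main study and sub-studies, are classified for analysis on one cut-off in one unit. Which one is for the study team to settle. The UCD values are quantitative, so this is a recode.
- For sub-study participants whose second test lay between the two cut-offs and who therefore had no third test, report a sensitivity bound: all third tests taken as negative, then all as positive.
- Add to Primary outcomes that confirmed positives, elaborate-screening participation and yield, and the matching cost inputs count only persons who reached confirmation through a positive first test at the main-study cut-off. A negative first test still completes home-based participation.
- Flag persons who reached further testing or the elaborate screening through either sub-study, and report them separately.

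The cost is two sentences, one flag variable and a small sensitivity analysis. The article describes data collection as ongoing, so the definitions can still be settled before the comparison is made. Third tests that were not sent remain missing, which is why the bound is needed.
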